## Assignment of interventions: allocation

### Sequence generation

All patients will be randomized to one of the following four groups at a 1:1:1:1 ratio one day prior to surgery: P0 (*n* = 33), P25 (*n* = 33), P50 (*n* = 33), and P75 (*n* = 33) groups. The assignment will be conducted by computer-generated random sequence with block randomization, stratified by sex and age (< 65 and ≥ 65 years). Based on the potential risk of age and gender having an impact on the pain relief and side effect outcomes after surgery, as suggested by previous literature, we performed stratification accordingly [19]. To maintain an equal allocation of participants to each of the four treatment groups, we will use a block size of 4 (one allocation for each treatment group within a block). The generated sequence will be masked from the primary investigators and will be recorded in the randomization list.

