## Statistical methods

### Statistical methods for primary and secondary outcomes

The primary objective of this study is to compare the effect of different doses of pregabalin to placebo on pain relief and the need for additional analgesics during the 72-h period following surgery, at various time points. Additionally, the study aims to assess the incidence of adverse events during this period. Primary outcomes include the VAS pain score, total dose of IV PCA administered, and frequency of rescue analgesic administered. We will use the Kolmogorov–Smirnov test (K-S test) to assess the normality of the primary outcome measure. If the normality assumption is met, we will perform an analysis of variance (ANOVA) analysis; otherwise, we will use the Kruskal–Wallis test for comparison. We will use the Bonferroni’s method for conducting subgroup analysis to account for multiple comparisons. Categorical variables, such as the incidence and frequency of nausea and vomiting caused by IV PCA or the incidence of side effects (sedation, dizziness, headache, visual disturbance, and swelling), will be compared between the groups using the chi-squared test. Statistical analyses will be performed using SPSS 20.0 (IBM, Armonk, NY, USA). In all analyses, *P* < 0.05 will be taken to indicate statistical significance.

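### Randomisation is stratified by sex and age group, but the named tests ignore both; analysing by the strata is a free improvement in precision

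*Protocol article*

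**What the plan says.** Protocol article, Sequence generation: "The assignment will be conducted by computer-generated random sequence with block randomization, stratified by sex and age", with age cut at 65 years, which makes four strata. The reason given is "Based on the potential risk of age and gender having an impact on the pain relief and side effect outcomes after surgery". On blocks, "we will use a block size of 4", with one place per arm, so every complete block balances the four arms within its stratum.

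Protocol article, Statistical methods for primary and secondary outcomes: for the primary outcomes, "If the normality assumption is met, we will perform an analysis of variance (ANOVA) analysis"; "otherwise, we will use the Kruskal–Wallis test for comparison". Nausea, vomiting and side effects "will be compared between the groups using the chi-squared test". Bonferroni's method is named for multiple comparisons. Sex, age and stratum appear in none of these. The section on additional analyses says that none is planned, so no adjusted analysis is provided elsewhere in the article.

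**The concern.** Balancing the arms within strata removes the variation between strata from the difference between arms. A test without the strata still counts that variation as error. Its standard error is then larger than the true sampling error of the comparison, so the test rejects a true null hypothesis less often than its nominal level and detects a real effect less often than it could.

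The article's own reason for stratifying is that these factors may affect the outcomes being tested. If that reason is right, the analysis gives up part of what the allocation scheme was set up to provide.

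**Working it through.** **Inputs.** From the article: four arms, 1:1:1:1, blocks of 4, four strata; 28 evaluable patients per arm (N = 112), 33 per arm randomised (132), 15% loss to follow-up; Cohen's f = 0.448, alpha 0.0167, power 0.95; group means 95.3, 96.6, 105.2 and a hypothetical 96.6, SD 10. Not in the article, so assumed: R², the share of within-arm variance explained by sex and age group, taken as 0, 5, 10 and 20%.

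**1. Reproduce the plan's figure.** One-way ANOVA with df 3 and N − 4, and noncentrality N·f². At N = 112 this is 112 × 0.448² = 22.48, df 3 and 108, and power 0.955. The next smaller multiple of four, N = 108, gives 0.946. So N = 112 reproduces exactly as an ANOVA with treatment group as the only factor. Dropout: 28/0.85 = 32.9, rounded up to 33.

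**2. Effect size from the listed means.** The mean of the four values is 98.425. The squared deviations are 9.77, 3.33, 45.90 and 3.33; their average is 15.58 and its root 3.95. With SD 10, f = 0.395. Results are shown at both 0.448 and 0.395.

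**3. Standard error.** Set the within-arm variance to 1. With exact balance within strata and n per arm, the difference between two arms has variance 2(1 − R²)/n, but the unadjusted model estimates it as about 2/n. The ratio of standard errors is 1/√(1 − R²): 1.000, 1.026, 1.054 and 1.118 for R² = 0, 5, 10 and 20%.

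**4. Actual level of the four-group test.** The 5% critical value of F(3, 108) is 2.689. Under exact balance the unadjusted F statistic is shrunk by about (1 − R²), so the actual level is about P(F > 2.689/(1 − R²)): 5.0, 4.2, 3.4 and 2.1%. Dropout disturbs the balance and moves the level part of the way back. Simulation with 132 randomised in stratified blocks of 4 and 15% random dropout gives the third column below. The adjusted test stays near 5% throughout.

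**5. Power.** The same simulated design at alpha 0.0167, with and without the strata in the model.

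| Assumed R² | Level of unadjusted 5% F test, exact balance | Same, with 15% dropout | Power gained by adjusting, f = 0.448 | Power gained, f = 0.395 | Excess width of any unadjusted interval |
|---|---|---|---|---|---|
| 0% | 5.0% | about 5% | about 0 points | about 0 points | 0% |
| 5% | 4.2% | about 4.1% | about 1 | about 2 | 3% |
| 10% | 3.4% | about 3.7% | about 2 | about 3 | 5% |
| 20% | 2.1% | about 2.5% | about 2 | about 6 to 7 | 12% |

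The simulated columns carry Monte Carlo error of a few tenths of a point in the level and up to about one point in the power differences. That explains why the dropout figure at 5% is not above the exact-balance figure.

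**The case against.** **This is detail for the analysis plan.** The article says only ANOVA, which can carry further factors, and covariates are often left to an analysis plan that is not shown. This has some force for the ANOVA. It has less for Kruskal–Wallis and the chi-squared test, which are named and have no place for a stratum. The sample size also reproduces as a one-factor ANOVA. The tests are fixed, not left open.

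**The loss is small.** This stands. In a simulation of 112 patients without dropout, unadjusted power at f = 0.448 was 95.6, 96.0 and 96.4% for R² of 5, 10 and 20%, at or above the planned 95%. A reader might infer that the whole benefit of stratifying is thrown away or that the trial is underpowered for this reason. The documents support neither: the comparison itself is still more precise, and only the estimate of its error is too large. The loss grows if the true effect is smaller than planned.

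**Stronger readings that fail.**
- A reader might infer bias or false positives. The error runs the other way.
- A reader might infer that the planned confidence intervals are too wide. The article plans none, so the width figures apply only to intervals later derived from the unadjusted model.
- The approximation 2(1 − Φ(1.96/√(1 − R²))) gives 4.4, 3.9 and 2.8% for R² of 5, 10 and 20%. It describes a single two-arm contrast, not the four-group test that is planned.
- The article calls the effect of age and sex a potential one. It does not say that an effect is expected, and R² could be near zero.
- None of these figures carries over to the binary outcomes, for which no gain was computed.

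**Conclusion.** The point holds as a free improvement, not as an error that threatens the trial's conclusions. The article stratifies by two factors, gives a reason that concerns the tested outcomes, and then names tests that ignore them. The direction is certain: the unadjusted tests are conservative whenever sex and age predict the outcome, and never the reverse.

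The size depends on an R² that the documents do not give. Over an assumed 0 to 20%, the adjustment is worth roughly 0 to 2 power points at the planned effect size and 0 to 7 points at the effect size implied by the listed means and SD. At R² = 0 it gains nothing and costs almost nothing. These figures apply to the linear model with additive stratum effects, strata of roughly equal size and dropout at random.

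**What to change.** Specify the following before unblinding:

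- **Continuous primary outcomes:** a linear model with treatment group, sex and age group (<65, ≥65) as fixed effects. This uses 2 df as main effects, or 3 df if the four strata are entered as one factor.
- **If a rank test is kept:** a stratified multi-group rank test for the four-arm comparison (generalised van Elteren, that is, a stratified Cochran–Mantel–Haenszel test on rank scores). The usual van Elteren test compares two samples, so it fits each dose against placebo but does not replace the four-group Kruskal–Wallis test.
- **Nausea, vomiting and common side effects:** a Cochran–Mantel–Haenszel test stratified by sex and age group. For rare events, use an exact unadjusted test.

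The cost is wording only. Both factors are known for every patient at randomisation, no further data or patients are needed, and clinical conduct does not change.

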### Trial design

This will be a single-centre, randomized, prospective, double-blind, superiority clinical trial with four arms. The trial will include three treatment arms where pregabalin will be administered at different doses (25, 50, 75 mg), and one control arm where placebo will be administered. The participants will be equally distributed among the four arms.

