### Outcomes

We will examine the efficacy of pregabalin on postoperative pain using the variables described in the literature [12]. The primary outcomes are pain intensity measured on a visual analogue scale (VAS) (length, mm), total administered amount of IV PCA measured (volume, mL), and frequency of rescue analgesics administered (the number of administrations, according to the type of rescue analgesic, and the total amount of morphine equivalent dose). The VAS score is evaluated using a pain ruler marked from 0 (no pain) to 100 (maximal pain) mm, with patients directly indicating their pain level. The secondary variables are the incidence and frequency of nausea and vomiting caused by IV PCA. Assessments of all variables will be performed during the first 72 h following the arrival of the participant at the general ward, subdivided into four periods: 1–6 h, 6–24 h, 24–48 h, and 48–72 h. We will evaluate pain between the midpoint and the end of each of the four time zones, aiming to measure as close to the end time as possible and use the pain scores at all four time points as the primary outcome. The pain levels in each time zone will be compared to see if they differ depending on the treatment method. Through this, we will ascertain how the treatment effect changes over time and how these changes differ among different treatment groups. Through these variables, we plan to check the effects of pregabalin on reduction of postoperative pain and IV PCA usage. In addition, we will examine whether reduction of IV PCA usage has a beneficial effect on the patient by reducing the incidences of common side effects, nausea and vomiting.

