### Sample size

The prior calculation of the sample size indicated that at least 28 subjects were required for each group. For calculation, the software G*Power 3.1.9.7 was used with a statistical power of 0.95 at an effect size of 0.448 with an alpha level of 0.0167. The effect size was determined based on a previous study [18]. In this study, three groups—those treated with placebo, pregabalin 75 mg, and pregabalin 150 mg—each comprised 28 participants. The groups were compared based on their PCA usage, with mean values of 95.3, 96.6, and 105.2 respectively, and an approximate standard deviation of 10. For the purposes of this study, which involves four instead of three groups, a fourth hypothetical group was considered with the mean value of 96.6, which is the median value of the three established groups. Based on this data, Cohen’s *f* was calculated, resulting in an effect size of 0.448. To compare the four groups through Bonferroni’s test, the alpha level was set at 0.05 divided by 4, which is 0.0167. When calculated based on these parameters, the total sample size needed is found to be 112, and the number of participants needed per group is 28. Considering a follow-up loss of approximately 15%, 33 participants per group would be required, resulting in a total of 132 participants needed for the study.

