### Methods for additional analyses (e.g. subgroup analyses)

No additional analyses are planned.

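### The primary objective is dose versus placebo, but the analysis fixes a four-arm omnibus test and a Bonferroni step whose set of comparisons is not stated

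*Protocol article*

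**What the plan says.** The Trial design section describes a "superiority clinical trial with four arms", three of them pregabalin doses and one placebo. The section on statistical methods for primary and secondary outcomes opens with the objective: "The primary objective of this study is to compare the effect of different doses of pregabalin to placebo on pain relief".

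The same section then fixes the test: "If the normality assumption is met, we will perform an analysis of variance (ANOVA) analysis; otherwise, we will use the Kruskal–Wallis test for comparison". The one sentence on comparisons between individual arms is "We will use the Bonferroni’s method for conducting subgroup analysis to account for multiple comparisons".

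Three other places bear on that sentence:
- The Sample size section begins its alpha calculation with "To compare the four groups through Bonferroni’s test". It divides 0.05 by 4 and gives the result as 0.0167.
- The Outcomes section says "The pain levels in each time zone will be compared to see if they differ depending on the treatment method", without saying which treatments are set against which.
- The section on additional analyses, whose heading gives subgroup analyses as its example, says "No additional analyses are planned".

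**The concern.** The null hypothesis of a four-group ANOVA or Kruskal-Wallis test is that all four arms are alike. It can be rejected because two doses differ from each other, so rejecting it does not answer whether any dose differs from placebo. The answer has to come from the arm-level step, and there the article leaves the set of comparisons open. Bonferroni could cover six pairs (all arms) or three (each dose against placebo), and the printed divisor of 4 matches neither.

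Two things are at stake. First, a borderline dose-placebo result can be significant with one set of comparisons and not with the other. Second, if all six pairs are meant, half of the alpha goes to dose-versus-dose pairs, and the comparisons in the stated primary objective lose power. The point concerns the choice of arm contrasts within one outcome at one time. The number of outcomes and periods is a separate matter.

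**Working it through.** **Inputs.** From the Sample size section: 28 evaluable participants per arm (112 in total), effect size f = 0.448 (taken as printed), alpha 0.0167, power 0.95. From the Statistical methods section: the objective, the omnibus test, and Bonferroni without a stated number of comparisons. Assumed here: two-sided tests, a normal outcome, equal SD in all arms, and true differences of 0.75 SD and 0.9 SD between 75 mg and placebo.

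**Step 1: what the stated sample size powers.** For a one-way ANOVA with four groups, power = P[F(3, N−4; λ) > F critical], with λ = N × f².
- N = 112: λ = 112 × 0.448² = 22.48, critical F = 3.56, power 95.5%.
- N = 108 gives 94.6%, so 112 is the smallest multiple of four that reaches 95%.

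The printed figure is reproduced as the power of the omnibus F test. It is not the power of any dose-placebo contrast.

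**Step 2: the possible Bonferroni levels.** Three placebo contrasts: 0.05/3 = 0.0167. Six pairs (4 × 3/2): 0.05/6 = 0.0083. The printed divisor: 0.05/4 = 0.0125. The printed value agrees with three comparisons and the printed divisor does not, so the section cannot be used to decide.

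**Step 3: smallest significant dose-placebo difference.** With pooled variance on 112 − 4 = 108 df, the standard error of a difference is √(2/28) = 0.267 SD. The threshold is the critical t × 0.267. The Dunnett critical value was obtained by simulation.

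| Procedure | Per-contrast alpha | Critical t | Threshold |
|---|---|---|---|
| Dunnett, three contrasts | 0.019 | 2.38 | 0.64 SD |
| Bonferroni, three contrasts | 0.0167 | 2.43 | 0.65 SD |
| Bonferroni, six pairs | 0.0083 | 2.69 | 0.72 SD |

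**Step 4: power for 75 mg against placebo.** Power = P[noncentral t(108; δ/0.267) > critical t]. The noncentrality is 0.75/0.267 = 2.81 and 0.9/0.267 = 3.37.

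| Procedure | δ = 0.75 SD | δ = 0.9 SD |
|---|---|---|
| Dunnett | 66% | 84% |
| Bonferroni, three contrasts | 65% | 82% |
| Bonferroni, six pairs | 55% | 75% |

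Against Dunnett, six-pair Bonferroni loses 11 and 9 points. Three-contrast Bonferroni loses 1 to 2.

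**Step 5: how often the omnibus test misleads by itself.** This was simulated with the F test at 0.05, counting trials in which F is significant but no Dunnett contrast with placebo is.
- No true differences: 38% of the 5% of trials with a significant F, or 1.9% of all trials.
- Linear dose-response reaching 0.75 or 0.9 SD at 75 mg: 3.9% or 2.5% of trials.
- Only the 75 mg dose works (0.75 or 0.9 SD): 16% or 10%.
- All doses equally effective: about 0.1% or less.

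**The case against.** ANOVA followed by Bonferroni is a conventional and valid procedure, and much of the case against this point stands.

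- **Error control.** A reader might take 'subgroup analysis' literally, note that no subgroup analysis is planned, and infer that the arm pairs are tested with no correction and an inflated false-positive rate. The documents do not support this. The sentence itself says Bonferroni is there to account for multiple comparisons, and the Sample size section applies it to the four groups. The phrase is loose wording for comparisons between arms. On either count of comparisons the family-wise error is controlled within one outcome and time point.
- **The omnibus mismatch.** It would be easy to build a case in which F is often significant with no dose-placebo difference, for example with doses lying on opposite sides of placebo. Under a plain linear dose-response it happens in only about 4% or 2.5% of trials.
- **Dose-versus-dose comparisons have a purpose.** The abstract and discussion speak of finding the optimal dose, and the Outcomes section asks how change over time differs among the treatment groups. These comparisons should not be discarded.
- **The value 0.0167.** If it records an intention to test three placebo contrasts, the power loss nearly vanishes.
- **Detail left to a fuller document.** A list of contrasts often appears in the analysis plan, which is not shown. That would dispose of a mere omission. Here, however, the article fixes a test that does not answer its stated objective, uses a wrong term for the step that would answer it, and gives an alpha whose divisor and value disagree.

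**Conclusion.** The point stands as a mismatch between objective and test, together with an unstated set of comparisons. The Statistical methods section asks "to compare the effect of different doses of pregabalin to placebo on pain relief" but names no contrast that answers it, and the Sample size section leaves open whether three or six comparisons are meant.

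The cost depends on which was intended. With six pairs, power for 75 mg against placebo falls from 66% to 55% at 0.75 SD and from 84% to 75% at 0.9 SD. With three contrasts at 0.0167 the fall is 1 to 2 points. These figures assume 28 per arm, a normal outcome with equal SD, two-sided tests and the stated true differences, which are illustrative and not taken from the protocol.

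It would go too far to say that the trial has uncontrolled error across arms or that its analysis is invalid. The defect is that the analysis is not matched to the stated objective and, on the usual post hoc reading, spends power on other comparisons. It should be corrected.

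**What to change.** In the section on statistical methods for primary and secondary outcomes:

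1. Name P25 v P0, P50 v P0 and P75 v P0 as the primary contrasts within each primary outcome and time point.
2. Test them directly with Dunnett's procedure at a two-sided 5% family-wise level, without first requiring a significant omnibus test. If the rank-based branch is kept, use the three rank comparisons with placebo, adjusted by Holm or Steel.
3. Report differences from placebo with simultaneous 95% intervals.
4. Replace 'subgroup analysis' with 'pairwise comparisons with placebo'.
5. Keep the omnibus test and the dose-versus-dose pairs as secondary, so that the optimal-dose question is still addressed.

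The alpha statement in the Sample size section should then be brought into line with the three contrasts.

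This changes wording only and needs no more patients or data. The one small downside is that dose-versus-dose differences are no longer part of the deciding family.

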**Assessments:**								
VAS score				X	X	X	X	X
IV PCA usage				X	X	X	X	X
Frequency of rescue analgesic use				X	X	X	X	X
Frequency of nausea and vomiting				X	X	X	X	X
Sedation				X	X	X	X	X
Dizziness				X	X	X	X	X
Headache				X	X	X	X	X
Visual disturbance				X	X	X	X	X
Swelling				X	X	X	X	X

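### The frequency of nausea and vomiting, most naturally a count per patient, is classed as categorical and tested with chi-squared, which costs power on a secondary outcome

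*Protocol article*

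**What the plan says.** The Outcomes section of the protocol article names two secondary measures: "The secondary variables are the incidence and frequency of nausea and vomiting caused by IV PCA". All variables are assessed over 72 h, "subdivided into four periods: 1–6 h, 6–24 h, 24–48 h, and 48–72 h". Table 2 schedules "Frequency of nausea and vomiting" at each postoperative time point.

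For this endpoint the article does not define frequency. For the other endpoint that uses the word, the same section does: "frequency of rescue analgesics administered (the number of administrations, according to the type of rescue analgesic".

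Under Statistical methods for primary and secondary outcomes, the primary outcomes, including the frequency of rescue analgesic, are compared by ANOVA if normality holds; "otherwise, we will use the Kruskal–Wallis test for comparison". Later in that paragraph come "Categorical variables, such as the incidence and frequency of nausea and vomiting caused by IV PCA", which together with the side-effect incidences "will be compared between the groups using the chi-squared test". The significance level is 0.05. How frequency would be laid out in a table is not stated.

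**The concern.** Incidence is categorical and chi-squared fits it. Frequency, listed beside incidence, must be something other than the yes/no measure. Given how the article uses the word for rescue analgesics, a number of episodes per patient is the natural reading.

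Pearson's chi-squared treats 0, 1, 2 and 3 episodes as unordered labels. It spreads its degrees of freedom over every kind of difference, whereas a dose trial looks for a shift towards fewer episodes. The test also needs independent units, so a table of episodes rather than of patients would be invalid if some patients are more prone to nausea than others.

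The Outcomes section says that the trial will examine whether lower IV PCA use benefits patients through less nausea and vomiting. At stake is the ability to see such a benefit in the number of episodes and, under one possible layout, the error rate of that comparison.

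**Working it through.** **1. Two similar measures side by side.**

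| Measure | Meaning given | Stated test |
|---|---|---|
| Frequency of rescue analgesic (primary) | number of administrations | ANOVA, or Kruskal–Wallis if not normal |
| Frequency of nausea and vomiting (secondary) | none; listed apart from incidence | chi-squared |

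No reason is given for the difference.

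**2. Number of patients.** The article gives no figure for this endpoint, so its own count of completers is used. One-way ANOVA with four groups, f = 0.448, alpha 0.0167 and power 0.95 reproduces the stated 28 per group, 112 in total (power 0.9547). 28/0.85 = 32.9, which rounds up to the stated 33.

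**3. Assumed inputs (not in the documents).** Episodes per patient follow a gamma-Poisson distribution with mean m and dispersion d, so the variance is m(1 + d·m). d = 0 means no clustering of episodes within patients. d is varied over 0, 0.5, 1 and 2. There are 2,000 simulated trials per scenario at nominal 0.05, so the Monte Carlo standard error is at most √(0.5 × 0.5/2000) = 0.011.

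**4. Power for means 1.5/1.2/1.0/0.6.** Loss is 1 − (power of chi-squared)/(power of Kruskal–Wallis).

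| d | Kruskal–Wallis | Grouped 0/1/2/3+ | Loss | Full count table | Loss |
|---|---|---|---|---|---|
| 0 | 0.790 | 0.590 | 25% | 0.464 | 41% |
| 0.5 | 0.553 | 0.364 | 34% | 0.197 | 64% |
| 1 | 0.389 | 0.242 | 38% | 0.104 | 73% |
| 2 | 0.253 | 0.155 | 39% | 0.055 | 78% |

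A second, separate simulation of the same scenario gave 0.81/0.55/0.38/0.25 for Kruskal–Wallis, 0.60/0.35/0.26/0.16 for the grouped table and 0.45/0.20/0.11/0.05 for the full table.

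With a larger assumed effect (means 2/1.5/1/0.5):

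| d | Kruskal–Wallis | Grouped | Loss | Full | Loss |
|---|---|---|---|---|---|
| 0 | 1.000 | 0.980 | 2% | 0.918 | 8% |
| 0.5 | 0.940 | 0.796 | 15% | 0.529 | 44% |
| 1 | 0.797 | 0.622 | 22% | 0.277 | 65% |
| 2 | 0.545 | 0.384 | 30% | 0.117 | 79% |

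**5. Type I error, mean 1.5 in every arm.**

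| Layout | d = 0 | 0.5 | 1 | 2 |
|---|---|---|---|---|
| Full count table | 0.038 | 0.028 | 0.024 | 0.011 |
| Grouped 0/1/2/3+ | 0.056 | 0.055 | 0.043 | 0.046 |
| Kruskal–Wallis | 0.061 | 0.052 | 0.043 | 0.043 |
| Incidence, chi-squared | 0.050 | 0.050 | 0.048 | 0.043 |
| Episodes pooled by arm | 0.059 | 0.222 | 0.383 | 0.566 |

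In the full count table 52% to 84% of expected cells are below 5, which goes with its conservative error rate.

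**6. Check of the pooled figures without simulation.** The pooled statistic is inflated by about 1 + d·m, so type I error ≈ P(χ²₃ > 7.815/(1 + d·m)).
- d = 0: 7.815/1 = 7.815, giving 0.050.
- d = 0.5: 7.815/1.75 = 4.466, giving 0.215.
- d = 1: 7.815/2.5 = 3.126, giving 0.373.
- d = 2: 7.815/4 = 1.954, giving 0.582.

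These agree closely with the last row of the table.

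**The case against.** A reader might infer that the plan must either inflate false positives or lose most of its power. The documents do not support that. No section says that episodes will be totalled by arm, so the inflated error rates belong to a layout that nobody has proposed, and even there they need clustering within patients, for which the article gives no figure. An ordinary grouped per-patient table fits the word categorical best. It keeps its error rate near 0.05 and gives up a quarter to two fifths of the power in the moderate scenario, and less with a larger effect. The largest losses come only from an uncollapsed table with clustered counts. All of this stands and limits the size of the point.

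It is also fair that frequency is not defined here, so a count of episodes is an inference, and that table layout is a detail an article may leave to the full protocol or SAP. But the test itself is not left open. The article names chi-squared for a measure that it lists apart from incidence, and no SAP detail about layout would make that test use the order of the counts.

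A reader might also infer that chi-squared is wrong for incidence. It is not: simulated type I error was 0.043 to 0.050 in the scenarios above, and the defect gives no reason to change that test.

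**Conclusion.** The point holds as a mismatch between measure and test. Chi-squared is assigned to what is most naturally a per-patient count, while the matching count in the same paragraph gets a suitable method. In the moderate scenario the likely cost is about 25–40% of the power of Kruskal–Wallis for a grouped table and about 40–80% for a full count table. Inflated type I error, about 20–57%, is a conditional risk that arises only if episodes are pooled by arm and cluster within patients at dispersion 0.5 to 2; without clustering it stays at about 5%.

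These sizes rest on 28 completers per arm and on assumed means and dispersion. The direction of the power loss does not depend on one setting: in every effect scenario run, both count tables had less power than Kruskal–Wallis. Only a secondary outcome is affected; the trial's primary conclusion is not. It should be corrected, but it is not a critical fault.

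**What to change.** In Statistical methods for primary and secondary outcomes, separate the two measures. Keep chi-squared for the incidence of nausea and vomiting, with one yes/no value per patient. Define frequency as one episode count per patient, and compare it by Kruskal–Wallis, as already planned for non-normal primary outcomes, or by negative binomial regression. Name one of the two before the data are unblinded.

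The cost is one sentence. It needs no extra patients and no change to clinical care. Table 2 already schedules the frequency to be recorded, so no new data are needed if the case report form holds the number of episodes.
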